**Fig 2 pone.0314548.g002:**
[figure not shown]
Process of the scale development, translation, and psychometric validation of the PROs-CP measures. Abbreviations: CFA, confirmatory factor analysis; EFA, exploratory factor analysis; IRT, item response theory; MCID, minimal clinically important difference; PROs-CP, Patients-Reported Outcomes among People Living with Chronic Pruritus.

Simultaneously, validated non-Thai version scales, namely—ItchyQoL, PUSH-D, and TAS-20 will be translated into the Thai-speaking language. The consecutive processes for scale translation are illustrated in Fig 1. Concisely, based on the permission from the authors of the original scales English version, the translation and cross-cultural adaptation will be performed in line with the standard guideline [30]. Two independent professional English-language translators will translate the measurement scale instructions and items from English into Thai. Of these, one person will be a board-certified dermatologist (MC), who is the study investigator and recognizes the study’s purpose and objectives, while the other layperson will not necessarily. Next, both translations will be combined by the two translators in conjunction with a team of experts who serve as independent observers. Any discrepancies that appear during this process will be resolved through team discussions.

Two independent bilingual native English speakers will independently blind-translate the synthesized measurement scales back into English. For the back-translation process, no translators had any medical health/dermatology background or acknowledged information regarding the particular original English version. To ensure that the translated version reflects the content of the original version, the content validity of the back-translation questionnaire will be reviewed and addressed. After that, both versions of the backward translations will be compared and reconciled with the original English version. To ensure equivalence between the original and translated Thai versions, conceptual equivalence (ensuring that words can hold the same conceptual meaning), item equivalence (individual items have the same relevance), and semantic equivalence (meaning of the items is the same in both version) will be employed. In the same manner as pilot testing and refinement of the scale development, a panel of experts and patients will review and refine the preliminary translated scales. Next, the EFA, non-parametric IRT, and initially psychometric analysis will be conducted to establish the validity, reliability, and scale stability (reproducibility) of the translated scales Thai version (i.e., ItchyQoL, PUSH-D, and TAS-20).

To track the treatment responses, the responsiveness of the pruritus-specific disease activity control (planned to develop through this study) and pruritus-specific HRQoL (using the ItchyQoL) in terms of the MCID will also be defined and established among patients with chronic pruritus. For scale interpretability in terms of MCID, we will incorporate both anchor-based and distributional criterion approaches using the change scales of disease activity and ItchyQoL at week 12 of follow-up [31–33].

Based on the consecutive recruitment of the open cohort, we plan to establish a temporal validation by using the same population at different times [15]. After a six-month and one-year follow-up, we will reanalyze sets of PROs-CP measurement tools to reaffirm the psychometric properties of the particular scale for people living with chronic pruritus over time. Cross-validity and reliability will be analyzed in order to establish the scale’s psychometric properties using an anchor-based questionnaire approach. Scale dimensionality for each multidimensional measurement tool will be reaffirmed using the confirmatory factor analysis (CFA) and non-parametric IRT methods. A quantitative method via face-to-face or video call using Zoom will also be employed. A random subsample (estimated approximately 50 patients) based on a one-on-one approach will be asked using structured and unstructured in-depth interviews to provide their perspectives on the face and content validity and relevancy of the PROs-CP tools. Moreover, based on feedback from patients and research personnel, the acceptability of scale measurement will be assessed through the study, along with the reasons for the unacceptability or unfavorable use of the PROs-CP measure in clinical practice.

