### Statistical analysis plan

All statistical analyses will be analyzed using Stata, version 16.0 (StataCorp, College Station, Texas). The significant level was tested at *P* value <0.05 based on hypotheses of two-tailed tests. Missing values will be handled with a multiple imputation method. Descriptive statistics will be analyzed and presented as number (%), mean (SD), or median (min–max) as appropriate.

Item analysis will be assessed descriptively and summarized along with the normality of score distribution, including skewness and kurtosis tests. The Kaiser-Meyer-Olkin measure and Bartlett test of sphericity will be tested to ensure the appropriate scale factor analysis of the measurement scales. For preplanned EFA, we will employ a principle factor extraction method, with the obliquely rotated using the Promax criterion. Eigenvalues with a criterion of >1.0 will be considered as the number of factors retained. The unidimensional set or subscales will be tested using a non-parametric IRT. The item characteristics curve analysis will be visualized to describe the characteristics of individual items within the particular scale. During the follow-up period, we will perform a CFA with a maximum likelihood estimation to reaffirm the scale structure. Specific fit indices will be tested, including the comparative-fit index (>0.900), non-normed fit index or Tucker-Lewis index (<0.900), standardized root mean squared residual (<0.100), and root mean square error of approximation (<0.100).

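### The follow-up CFA can confirm each scale's dimensionality at an occasion, but its absolute fit limits cannot support the claim that the scales hold their properties over time

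*Protocol article*

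**What the plan says.** In the Protocol article, the Study I section sets the aim of the rechecks: "we plan to establish a temporal validation by using the same population at different times", and, after six months and one year, "we will reanalyze sets of PROs-CP measurement tools to reaffirm the psychometric properties of the particular scale for people living with chronic pruritus over time". For the multidimensional tools the method is: "Scale dimensionality for each multidimensional measurement tool will be reaffirmed using the confirmatory factor analysis (CFA) and non-parametric IRT methods". The same paragraph adds anchor-based cross-validity, reliability, and interviews with about 50 patients on face and content validity.

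The Statistical analysis plan section gives the CFA criterion: "During the follow-up period, we will perform a CFA with a maximum likelihood estimation to reaffirm the scale structure". The limits are "Specific fit indices will be tested, including the comparative-fit index (>0.900), non-normed fit index or Tucker-Lewis index (<0.900") and "standardized root mean squared residual (<0.100), and root mean square error of approximation (<0.100"). The TLI limit is printed in the opposite direction to the CFI limit; it is read below as above 0.900.

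Scores are used as change in the MCID work, which combines anchor-based and distribution-based approaches "using the change scales of disease activity and ItchyQoL at week 12 of follow-up". Reproducibility is tested by an intraclass correlation, with a retest interval of 60 to 120 minutes (Study I). The one-year analysis compares pruritus-intensity groups and names no within-patient change.

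**The concern.** A claim that a scale keeps its properties over time, and any use of its change score, requires the items to relate to the underlying state in the same way at both occasions: equal loadings and equal intercepts (or thresholds). The stated criterion looks at absolute fit and compares nothing between occasions.

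If patients recalibrate some items after months of care, the total moves although their state has not changed, and the recheck still passes. The shift would then enter the statement that the properties were reaffirmed and, if present by week 12, the change scores that define the MCID. Responsiveness is part of the first primary objective and the MCID is a secondary objective. The week-12 change scores also precede the first recheck at six months, so no step stated in the article tests comparability at week 12.

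**Working it through.** The article gives no figure for measurement stability, so there is nothing to reproduce. Its target of 396 with 20% missing responses is used only to set n: 396 × 0.8 = 316.8, taken as 317.

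**Assumed inputs, not in the article:** 10 items with unit variance, one factor, loadings 0.7 (residual variance 1 − 0.49 = 0.51), factor correlation 0.6 between occasions, same-item residual correlation 0.3, no true change.

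**Step 1: why the fit limits cannot see drift.** Adding a constant to a continuous item leaves the item covariance matrix unchanged, so CFI, TLI, SRMR and RMSEA are unchanged. Loadings are estimated afresh at each occasion, so a changed loading is absorbed by the model.

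**Step 2: size of the spurious change.**
- Variance of the total: (10 × 0.7)² + 10 × 0.51 = 54.1; SD = 7.36.
- Four items shifted by 0.5: 4 × 0.5 / 7.36 = 0.27 SD.
- Variance of the paired difference: 2 × 49 × (1 − 0.6) + 2 × 5.1 × (1 − 0.3) = 46.34; SD = 6.81.
- Paired test at n = 317: (2.0 / 6.81) × √317 = 5.2, so the spurious change is almost always significant.

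**Step 3: simulation** (200 runs per scenario, n = 317, limits applied at follow-up).

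| Scenario, no true change | Passes fit limits | Alpha | Scalability H | Change in total (SD) |
|---|---|---|---|---|
| No drift | 100% | 0.905 | 0.492 | 0.00 |
| 4 of 10 items +0.5 SD | 100% | 0.904 | 0.488 | 0.27 |
| Same, five-category items | 100% | 0.89 | 0.477 | 0.26 |
| 4 loadings 0.7 to 0.4 | 100% | 0.861 | 0.390 | 0.00 |

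The spurious change in the second and third rows was significant in every run. Results at n = 396 were the same in substance. In a separate simulation of 500 runs per level, 5 of 10 items drifting by 0.3, 0.4 or 0.5 SD gave 0.21, 0.27 and 0.34 SD, again with 100% passing. Correlations with an anchor do not change when a constant is added to a score.

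**Step 4: what the limits do catch.** When four items split onto a second factor, 0% passed with factor correlation 0.4 or 0.6; 91.5% passed at 0.8.

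**Step 5: would an invariance test see the drift?** For a two-occasion model with equal loadings and intercepts, the likelihood-ratio test of intercepts has 9 df and non-centrality (n − 1) × F0, where F0 is the population misfit. The population CFI drop is about F0 / 9.99, where 9.99 is minus the log determinant of the 20-variable correlation matrix under the inputs above (baseline model with free means).

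| Drift | F0 | Power, n = 317 | Power, n = 100 | CFI drop |
|---|---|---|---|---|
| 4 items, 0.5 SD | 0.7743 | 1.00 | 1.00 | 0.078 |
| 1 item, 0.5 SD | 0.2749 | 1.00 | 0.98 | 0.028 |
| 4 items, 0.2 SD | 0.1326 | 0.999 | 0.71 | 0.013 |
| All 10 items, 0.5 SD | 0 | 0.05 | 0.05 | 0 |

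The last row is a limit of the method: a uniform shift of equally loading items looks exactly like true change.

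**The case against.** - **The CFA is offered for dimensionality, which it can test.** This stands. No sentence says that CFA fit alone establishes stability. But dimensionality is the part of the recheck given explicit limits, and the stated aim of that recheck is psychometric properties over time.
- **Other checks are planned.** Partly stands. The interviews might reveal changed item meaning, and the item characteristic curves were not simulated. Alpha, scalability and anchor correlations do not show intercept drift, and a retest within two hours says nothing about months.
- **An invariance step may sit in the full protocol or analysis plan.** Possible; only the article is at hand, and its list of indices is not closed. The point therefore rests on the criterion the article states, not on what it omits.
- **The temporal validation may mean later recruits rather than the same patients.** The wording allows this. In that case within-patient stability would not be examined at all, while the week-12 change scores still depend on it.
- **The size is built in by assumption.** Correct. The article gives no evidence that drift will occur. The simulation shows what the limits would miss, not how much drift to expect.
- **A reader might infer that all response shift would pass and reach the one-year results as patient change.** The documents do not support this. A change of structure is usually caught, and the one-year analysis compares intensity groups, so drift common to all groups largely cancels.
- **The MCID is not wholly exposed.** This stands. A constant shift does not alter the spread used by distribution-based estimates. An anchor-based estimate is exposed if it is a mean change within one anchor category, and less so if it is a difference between categories; the article does not say which.

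**Conclusion.** The point holds in limited form. The follow-up CFA criterion can support a statement about dimensionality at each occasion. It cannot support the wider conclusion that the scales keep their properties over time, and it gives no assurance for the week-12 change scores. If drift occurs, the effect could be material: about 0.27 SD on the total for 4 of 10 items shifted by 0.5 SD, with every run passing the fit limits. That figure rests on the assumed item count, loadings and drift and on reading the TLI limit as above 0.900. It is an illustration, not a forecast. It is worth correcting because the remedy is cheap and the claim concerns a primary objective.

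**What to change.** Keep the CFA and its limits for dimensionality. Add pairwise longitudinal invariance tests: baseline with week 12, with six months, and with one year, in patients with both occasions. Allow correlated residuals for the same item, and test equal loadings, then equal intercepts or thresholds (for example, a CFI drop of no more than 0.010).

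Claim stability over time only for scales with at least partial invariance. Where it fails, report a sensitivity MCID from the partially invariant model or without the drifting items, beside the raw-change MCID. If this is not wanted, limit the Study I claim to dimensionality at each occasion. If the full plan already contains such a step, one sentence saying so is enough.

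Pairwise models are preferable to one model of all four occasions. With 17 items (PUSH-D) to 20 items (TAS-20), four occasions give 68 to 80 indicators. Applying the plan's minimum of 5 patients per question to each indicator, that needs 340 to 400 patients, above 317. Two occasions give 34 to 40 indicators, or 170 to 200 patients.

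Cost: a few lines of text and some extra model fitting on data already planned. Some scales may be reported as only partially invariant, and a uniform shift of all items still cannot be told from true change.

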### Study II: Patient perspectives on living with chronic pruritus

In this sub-studies, we will perform a qualitative study to explore the views and experiences of patients living with chronic pruritus. Regarding the purposive sampling, the subsample of eligible patients will be invited through the participating open cohort recruiting. Ultimately, we plan to include patients based on maximum sample variation using key clinical characteristics (i.e., primary skin diseases, severity of symptoms, and burden or impact on daily life) to represent and reflect the perspective of people living with chronic pruritus. For convenience, either face-to-face or video calls using Zoom will be considered. A trained research assistant will conduct one-on-one qualitative interviews using structured and unstructured questions among Thai-speaking aged 20 years or older with chronic pruritus (approximately 60–120 min). Patients will be asked about the burden of chronic pruritus (e.g., which associated symptoms of pruritus they experienced and considered to be the worst), problems and concerns of how pruritus affected their lives, treatment benefits/responses, barriers/facilitators to achieving disease control, patient preferences, and how their perceived satisfaction with treatment care. As a part of quality control, lead investigators (SN and MC) will monitor the quality of the interview process and transcript and provide feedback to an interviewer as necessary.

### Study III: Longitudinal cohort and health outcomes

Based on an open registered cohort approach, eligible patients will be recruited continually to identify interested patients who intend to participate in the PROs-CP study. All patients will be monitored based on routine follow-up with a standard visit at outpatient clinics (approximately every 2–3 months). Data will be collected through the study follow-up periods every 2–3 months onwards, including pruritus characteristics and medical history (i.e., primary skin diseases, duration and localization of itch, IFSI classification and category of underlying skin disease, and symptoms associated with pruritus, comorbid conditions), physical examination, routine laboratory tests, sets of PROs measurement tools, treatment for specific-pruritus and non-pruritus, and healthcare utilization (i.e., direct medical costs, direct non-medical costs, and indirect costs). To facilitate longitudinal cohort retention and minimize missing data, various reminder strategies based on our routine follow-up care, case manager staff members will contact the eligible patients/caregivers through their preference contact approaches (i.e., phone, text message, or direct email) within 1–3 days before the visiting follow-up or anticipate data collection date.

All patients will be monitored for as long as possible. However, we plan to assess the severity and symptoms of pruritus, disease activity control, and longitudinal impact on health outcomes at one year of follow-up. These will include the impact of chronic pruritus and disease activity on long-term PRO outcomes (i.e., HRQoL, symptoms burden, and mental health and psychosocial issues), health utility, safety profiles (adverse events), hospitalization and healthcare visit, and healthcare expenditures (direct medical costs, direct non-medical costs, indirect costs, and out-of-pocket costs).

### Data management and security

Based on deidentified data, all data elements in this study cohort will be incorporated with the local joint data (electronic health records—outpatient and inpatient information and Pharmacy Dispensing and Laboratory Support System extract), as well as transcript data from the qualitative method will be entered continually into the PROs-CP database via the REDCap^TM^ platform. However, the patient’s identification information (i.e., name, telephone number, home address, email address, social media contacts, and family/caregiver member information) will not be entered into the database to protect the patient’s privacy.

The external panel of two health information technicians from the Pharmacoepidemiology and Statistics Research Center will verify, cross-check, and monitor all data elements throughout the study follow-up periods to maintain high-quality information on the PROs-CP database. Moreover, two data administrators will be checked for completeness and consistency with the source documents in a timely manner to minimize data errors and missing values. All data elements in the PROs-CP database will be managed and encrypted using a password code, which only the assigned management team can access to view and edit.

### Sample size estimation

Although we plan to include all eligible patients in this open longitudinal study, a pre-specified sample size for scale development and validation of the PRO-CP measurement tool was estimated. As such, sample size consideration for this study will be calculated based on two parameters. Firstly, we use a sample-to-item ratio (5–15 patients per question for both the EFA and CFA approach) to address a scale structure for factor analysis [8, 28, 29]. Secondly, a fair correlation coefficient statistic (>0.30) with anchor-based questions was used to establish convergent validity [34]. Regarding a power of 80% and 0.05 type I error, a minimum target of 396 patients with chronic pruritus is needed for this study cohort to account for missing responses of 20% during the cohort follow-up.

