**Aspect of mental health, psychosocial, and psychosomatic symptoms**			
PHQ-9	Yes	Yes	• The PHQ-9 consists of 9 items to measure depressive symptoms (total score ranges from 0 to 27). • This scale showed excellent psychometric properties, with a Cronbach’s α of 0.90 among the general population in Thailand [29, 47]. • A cut-off point ≥9 was considered to indicate depressive symptoms [48].
GAD-7	Yes	Yes	• The GAD-7 consists of 7 items to measure anxiety symptoms (total score ranges from 0 to 21). • This scale had excellent psychometric properties, with a Cronbach’s α of 0.90 among the general population in Thailand [29, 47]. • A cut-off point ≥8 was considered to indicate depressive symptoms [49].
WHO-5 well-being index	Yes	Yes	• The WHO-5 well-being index consists of 5 items to measure health-related personal well-being. • This scale had excellent psychometric properties, with a Cronbach’s α of 0.91 among the general population in Thailand [29, 47]. • A cut-off point <50 was considered a low well-being index [47].
BRCS	Yes	Yes	• The BRCS consists of 4 items to measure cope tendencies with psychological stress (total score ranges from 4 to 20). • This scale had excellent psychometric properties, with a Cronbach’s α of 0.84 among the general population in Thailand [29].
TAS-20	Yes	No: translated and psychometric testing through this study	• The TAS-20 consists of 20 items to measure alexithymia (difficulty in identifying and describing emotions) [27]. • The non-Thai version showed adequate psychometric properties in 30 different languages (or dialects of the same language) [26].
PUSH-D	Yes	No: translated and psychometric testing through this study	• The PUSH-D is a dermatologic-specific scale to evaluate stigmatization in patients with visible skin conditions, which consists of 17 items [16]. • This scale demonstrated excellent psychometric properties, with Cronbach’s α 0.94 [16].
RSES	Yes	Yes	• The RSES consists of 10 items to measure self-esteem and is widely used in social science research. • The revised Thai RSES scale demonstrated excellent psychometric properties, with Cronbach’s α ranging from 0.84 to 0.86 [50].
UCLA Loneliness Scale-6	Yes	Yes	• The short version of the UCLA loneliness scale consists of 6 items to gauge loneliness levels. • This scale revealed acceptable psychometric properties in both non-clinical and clinical settings, with Cronbach’s α ranging from 0.72 to 0.84 [51].

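### The 396-patient target is tied to 80% power, but the stated correlation needs about 107; the figure appears to come from the sample-to-item ratio

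*Protocol article*

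**What the plan says.** The Sample size estimation section names two bases for the target. The first is a respondent-to-item ratio for factor analysis: "5–15 patients per question for both the EFA and CFA approach". The second is a correlation: "a fair correlation coefficient statistic (>0.30) with anchor-based questions was used to establish convergent validity". It then gives one number for both, opening with "Regarding a power of 80% and 0.05 type I error" and going on to conclude that "a minimum target of 396 patients with chronic pruritus is needed for this study cohort to account for missing responses of 20" percent, where the missing responses are those that arise in follow-up.

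The Statistical analysis plan section sets significance testing at 0.05 "based on hypotheses of two-tailed tests".

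The article does not give the number of items used, the ratio chosen within 5 to 15, the number before inflation, the null value of the correlation, or how the 20% was applied. It does not say which basis produced 396.

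**The concern.** A respondent-to-item ratio has no power and no type I error. The sentence that attaches both to 396 can therefore refer only to the correlation. A reader will take it that 396 patients give 80% power to detect a correlation of 0.30 after 20% missing responses, and the inputs do not give that.

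This is the only sample-size justification in the article, and it supports the first primary objective, the psychometric validation of the measures. If the stated power does not belong to the stated number, nobody can tell which requirement governs recruitment, or what is lost if recruitment falls short.

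**Working it through.** **Inputs.** From Sample size estimation: power 80%, type I error 0.05, correlation 0.30, ratio 5 to 15 per item, 20% missing. From Statistical analysis plan: two-tailed tests. From Table 2: PUSH-D has 17 items and TAS-20 has 20. Assumed: a null correlation of 0, and 22 items for ItchyQoL (top score 110 divided by an assumed 5 points per item).

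**1. Trying to reproduce 396 from the power inputs.** By Fisher's z:

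n = ((1.960 + 0.842) / atanh(0.30))² + 3 = (2.802 / 0.3095)² + 3 ≈ 84.9, so 85.

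Allowing for 20% missing: 85 / 0.8 = 106.3, so 107 enrolled (102 if multiplied by 1.2). The stated target is 396 / 107 = 3.7 times this.

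Other settings do not close the gap:

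| Setting | n | n / 0.8 | n × 1.2 |
|---|---|---|---|
| One-sided, 80% power | 68 | 85 | 82 |
| Two-sided, 90% power | 113 | 142 | 136 |
| Two-sided, 95% power | 139 | 174 | 167 |
| Two-sided, 80% power, Bonferroni for 30 tests | 169 | 212 | 203 |

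A null of 0.30 comes near 396 (409 or 393) only with an unstated alternative of about 0.42 and a one-sided test, which conflicts with the stated two-tailed testing.

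**2. Power that the target actually gives.** 396 × 0.8 = 316.8, about 317. For a correlation of 0.30 against 0:

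Φ(0.3095 × √314 − 1.960) = Φ(3.52) ≈ 0.9998, above 99.9%.

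With 317 patients, 80% power corresponds to a correlation of about 0.16, which the article does not mention.

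**3. Trying the item ratio.** At 15 patients per item:

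| Items | Base | Base / 0.8 | Base × 1.2 |
|---|---|---|---|
| 17 (PUSH-D) | 255 | 319 | 306 |
| 20 (TAS-20) | 300 | 375 | 360 |
| 22 (assumed, ItchyQoL) | 330 | 413 | **396** |

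The only exact match is 330 × 1.2. Other products also give 330, such as 33 × 10 and 66 × 5. Division would need a base of 316 or 317, and neither is a whole number of items times a whole ratio from 5 to 15.

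**4. Consequence if the base was 330.** Keeping 330 after 20% loss needs 330 / 0.8 = 412.5, so 413 enrolled, 17 more than 396 (17 / 413 = 4.1%). With 396 enrolled, 316.8 / 22 = 14.4 per item instead of 15.

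**The case against.** The strongest reply is that two bases are listed, the item ratio comes first, and taking the larger requirement is normal practice. Exceeding the power requirement harms nothing, and an article may leave the item count and pre-inflation number to the full protocol. This stands as far as it goes: the omitted details alone would not be a finding. It does not rescue the sentence that is printed, which attaches 80% power to a number that does not come from it.

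Three stronger readings are tempting, and the documents do not support them.

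- **That 396 leaves too few patients.** About 317 still gives 14.4 per item for an assumed 22 items, inside the protocol's own range. For the 17- and 20-item scales, 396 covers even 15 per item with correct division (319 and 375). The exploratory factor analysis belongs to initial scale development, before most follow-up loss, and missing values are to be multiply imputed, so 317 is not clearly the analysis set.
- **That multiplying by 1.2 is established.** Neither 330, nor 22 items, nor a ratio of 15 is stated. The ItchyQoL bands in Table 2 run from 0 to 110, which five-level items scored 1–5 or 0–4 cannot produce on 22 items. The new scales are still at item generation, so their lengths are unknown. The exact match is suggestive only.
- **That the study should be powered to show a correlation above 0.30.** The protocol plans coefficients with bootstrap intervals and nowhere requires the lower limit to exceed 0.30. That would be a new criterion, not an error in this one.

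**Conclusion.** The link between 396 and 80% power is wrong as written. On the stated inputs, with a null of 0, the correlation needs 85 patients, or 107 enrolled. The roughly 317 left from 396 give more than 99.9% power. This part does not depend on where 396 came from.

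That 396 comes from 22 items × 15 × 1.2 is the best-fitting explanation, but it is an inference that the sponsor must confirm. If it is right, the allowance was applied in the wrong direction and falls 17 patients (about 4%) short of the 413 needed to keep 330. No requirement stated in the article is missed. The point concerns the justification of the sample size, not its adequacy.

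**What to change.** Reword the last part of Sample size estimation, for example:

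> The target of 396 is set by the sample-to-item ratio for factor analysis ([number] items × [ratio] = [base] before allowance; sponsor to confirm). If 20% of responses are missing, about 317 patients remain, or [317 divided by the item count] per item, within the planned range of 5 to 15. Detecting a correlation of 0.30 against zero with 80% power at two-sided 0.05 needs 85 patients (107 enrolled), so power for that correlation exceeds 99.9%.

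If the base is confirmed as 330, either give the retained ratio as 14.4 per item for 22 items, or raise the target to 413 to keep 15.

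The cost is one paragraph. No extra patients are required: 396 already satisfies the stated range, and the cohort is open to all eligible patients. With 70 enrolled at the last report, the correction is easy to make now.
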